## Abstract

**Background:**

Recent reviews suggest that telemedicine solutions for patients with chronic obstructive pulmonary disease (COPD) may prevent hospital readmissions and emergency room visits and improve health-related quality of life. However, the studies are few and only involve COPD patients who are in a stable phase or in-patients who are ready for discharge. COPD patients hospitalized with an acute exacerbation may also benefit from telemedicine solutions. The overall aim is to investigate a telemedicine-based treatment solution for patients with acute exacerbation of COPD at home as compared to conventional hospital treatment measured according to first treatment failure, which is defined as readmission due to COPD within 30 days after discharge.

**Methods:**

COPD patients with acute exacerbation who fulfilled the eligibility criteria and were from two university hospitals in Denmark were randomized (1:1) by computer-generated tables that allocated treatments in blocks of four to receive either standard treatment at the hospital or the same standard treatment at home using telemedicine technology (that is, a video conference system with a touch screen and webcam and monitoring equipment (spirometer, thermometer, and pulse oximeter)). Patients treated in the telemedicine group were backed up by an organizational setting securing 24/7/365 online access to the hospital, as well as access to oxygen, nebulizer therapy, oral medical therapy and surveillance of vital parameters from home monitoring devices. Patients in both groups were discharged when clinically stable and when fulfilling five pre-specified discharge criteria. Follow-up was performed at 1, 3 and 6 months after discharge.

The primary outcome was treatment failure defined as readmission due to exacerbation in COPD within 30 days. Secondary outcomes were death from any cause, prescription of additional antibiotics or steroids, need of intubation or non-invasive ventilation, emergency room visits, visits to the general practitioner, lung function, bed days, health-related quality of life, healthcare costs and user satisfaction.

**Results:**

Enrollment of patients started in June 2010 and ended in December 2011. Follow-up ended in May 2012. Results were analyzed in 2013.

**Conclusions:**

The results may have implications on future hospital treatment modalities for patients with severe exacerbations in COPD where telemedicine may be used as an alternative to conventional admission.

**Trial registration:**

Clinical Trials NCT01155856

## Background

According to WHO (World Health Organization), chronic obstructive lung disease (COPD) will become the third leading cause of death worldwide in 2030 [1]. More than 430,000 people in Denmark are affected by COPD [2] - one of the highest prevalence’s in the world - and every year 23,000 hospital admissions are due to COPD [3]. Concomitantly with an aging population [4] the frequency of chronic disease is increasing and causing increases in healthcare costs which in turn has stimulated research and innovation in technology solutions [5].

Several initiatives supported by technology, among these telemedicine for patients with chronic disease, are tested to explore whether alternatives are, when used correctly, feasible and safe for the patient and cost-effective compared to conventional care [6].

Clinical evidence is a precondition for implementing telemedicine solutions into the clinical practice [7].

### Rationale

Recent reviews [7-10] with focus on telemedicine for COPD patients revealed very few randomized clinical trials (RCT’s), and the trials included in the reviews were small and multimodal with telemedicine as only part of the intervention, making it difficult to determine the effect of telemedicine alone. Furthermore the trials comprised data on newly discharged or stable COPD patients only.

The reviewers concluded that some telemedicine solutions for COPD patients may significantly reduce the number of hospital readmissions and emergency room visits [8,9] and may also have a positive effect on health-related quality of life [9]. A recent study examining the effect of telehealth on use of secondary care and mortality has found telehealth to be associated with lower emergency admission rates [6]. The study involved 3,230 patients with diabetes, chronic obstructive pulmonary disease, or heart failure who were recruited from practices in the UK. Evidence is, however, still poor and it is suggested that future trials involving telemedicine for COPD need to have improved designs and more rigorous attention to intervention specification and overall aim, to outcome definition, measurement and health-economic analyses [7]. It is also mentioned that there is no evidence that these interventions are embedded in routine clinical care [7]. In this article we describe the methods of The Virtual Hospital Trial (VHT) where we have endeavored to overcome aforementioned significant caveats in regard to design, intervention specification, outcome definitions etcetera, and, in addition, we describe how the intervention was embedded in the routine clinical care at the hospital.

### Purpose

The overall aim of this study was to investigate a telemedicine-based treatment solution for patients with acute exacerbation of COPD at home compared to conventional hospital treatment as measured by first treatment failure, which is defined as readmission due to COPD within 30 days after discharge. Use of additional medicine and healthcare services due to COPD, mortality rate, physiological parameters, and health-related quality of life, healthcare costs, adverse events and user satisfaction are also evaluated.

## Methods

### Design

This was a consecutive, randomized, open, parallel group, multicentre trial design. The study was planned as a PhD study with a duration of 3 years, starting with 18 months of enrollment (June 2010 to December 2011). All enrolled patients were followed for 6 months at follow-up visits 1, 3 and 6 months after discharge. Follow-up finished in May 2012.

### Study settings

Patients were recruited consecutively from the emergency departments at two University Hospitals in the area of Copenhagen, Denmark.

### Patients

#### ***Eligibility criteria***

The eligibility criteria are listed in Table 1. Patients who met the inclusion criteria and none of the exclusion criteria were consecutively enrolled in the trial. Staging of COPD was done according to the GOLD criteria, which is a global initiative and strategy for the diagnosis, management and prevention of COPD [11]. The severity grade was based on historical clinical data obtained through the patient records. Although the severity grade of COPD cannot be determined during an exacerbation, measurements were made prior to randomization to obtain baseline values and to confirm that the patients had a decreased, obstructive lung function in addition to a known diagnosis of COPD.

**Table 1 T1:** Eligibility criteria

**Inclusion criteria**	**Exclusion criteria**
• COPD GOLD stage III-IV (that is, FEV1/FVC <0.70 and FEV1 <50% of predicted value).	• Need of NIV or manual ventilation at time of randomization
• Acute exacerbation of COPD (for example, Anthonisen *et al*. definition [12]).	• Severely overweight^b^
• >45 years	• Serious comorbidity:
• pH >7.35	• Unstable heart disease^c^
• Compliance (see, hear, the ability to understand and carry out self-monitoring tasks).	• Poorly regulated diabetes^d^
• Expected hospitalization > 2 days^a^	• Malignancy
	• Other diseases/conditions that make participation impossible (dementia, delirium etcetera).
	• Temperature >38°C or need for IV antibiotics
	• Noncompliance (nursing home resident, tourist etcetera).
	• Participation in another trial

^a^judged by the attending doctor after initial acute management.

^b^severely overweight, causing immobility or Pickwick Syndrome.

^c^angina pectoris, changes in the electrocardiogram that needed immediate treatment during admission.

^d^need for additional insulin during admission.

*COPD* chronic obstructive pulmonary disease, *GOLD* the global initiative for chronic obstructive lung disease, *FEV1* forced expiratory volume in 1 second, *FVC* forced vital capacity, *NIV* non-invasive ventilation, *IV*, intravenous.

### Randomization

Consenting patients, who fulfilled the inclusion criteria and none of the exclusion criteria, were consecutively randomized. An external center-used computer generated tables to allocate treatments in fixed blocks of four and patients were randomized 1:1 to either intervention or control group. Each hospital was provided with sequentially numbered, sealed and opaque envelopes from the external center in batches of ten envelopes so that the allocation sequence was concealed from the investigators assessing and enrolling participants. The sealed envelope was not opened by the patient until after the patient had signed a written consent form. The allocation concealment mechanism was monitored closely by the investigators to ensure that envelopes were never resealed and to ensure patients were entered correctly in the study no matter what allocation the envelope revealed.

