### Implementation and organization of telemedicine technology at the acute emergency ward

For the first 9 months of inclusion it was the trial physicians and nurses from the telemedicine research unit at Frederiksberg Hospital who took care of the telemedical patients and operated the 24/7 ‘call center’. The research staff either stayed at the hospital during nights or contacted the patients from their own homes using a PC with the TT solution embedded. Later on, twenty experienced nurses working at the acute emergency department at Frederiksberg University Hospital were trained 4 hours each in operating the TT solution to take over the calls during evenings and nights. During the daytime the research unit remained on call. Nursing staff from the emergency department were instructed to treat the telemedical patients exactly the same way as they would treat them if they had been present at the hospital except from the physical contact, which of course was not possible.

Patients admitted to their own home were represented with a special color on the electronic patient boards in the acute emergency ward indicating they were not physically present in the acute emergency wards but that they were still admitted or ‘outmitted’, which became an everyday expression for a patient treated at home. At the organizational level, the bed in which the patient should have been placed in was kept empty to reflect a decrease in workload at the emergency ward having patients ‘outmitted.’ This was very meaningful in that the emergency staff did not feel as if further workload was being introduced as a result of new treatment modalities.

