### Statistics

All analyses will be done using SAS software version 9.3 http://support.sas.com/software/93. Time to readmission after discharge due to an exacerbation will be assessed using a stratified Cox regression to relax the assumptions of proportional hazards. Differences in readmission rate over time will be assessed using multilevel mixed-effects linear regression analysis with unstructured variance matrix where the baseline values of the outcomes are used as covariates. *P* values below 0.05 will be considered significant for the primary outcome, and *P* values below 0.01 will be considered significant for secondary outcomes. Skewed variables will be power transformed if possible; otherwise, the variables will be transformed into dichotomous responses. Missing values will be replaced using multiple imputations [17]. Survival times will be plotted in a Kaplan-Meier survival curve. Differences between the two groups in prescription of additional antibiotics or steroids due to further exacerbation, need of non-invasive ventilation or mechanical ventilation, emergency room visits, visits to the general practitioner, lung function, bed days, and adverse events will be analyzed with an unpaired Student t-test if data are normally distributed or Mann-Whitney test if not. All categorical data will be analyzed with Chi-square test or Fishers exact test as appropriate. For the health-related quality of life scores, differences from baseline, both within and between study groups, and 95% confidence intervals will be calculated. All analyses will be done on the principle of intention to treat.

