## Results

From June 2010 to December 2011, 57 patients were randomized. Average monthly recruitment for the trial was 3,2 patients. Follow-up visits ended in May 2012.

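### Envelopes were drawn separately at two hospitals, but the two-sample tests named for the secondary outcomes ignore hospital and the Cox stratum is not named

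*Protocol article*

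**What the plan says.** Study settings: "Patients were recruited consecutively from the emergency departments at two University Hospitals". Randomization: an external center used "computer generated tables to allocate treatments in fixed blocks of four and patients were randomized 1:1", and "Each hospital was provided with sequentially numbered, sealed and opaque envelopes from the external center in batches of ten envelopes". Each patient was thus allocated from an envelope set held at a known hospital. The article does not say whether the center prepared one blocked list per hospital or cut both hospitals' envelopes from a common list.

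Statistics: "Time to readmission after discharge due to an exacerbation will be assessed using a stratified Cox regression to relax the assumptions of proportional hazards". No stratum is named. A multilevel mixed model is also planned, without naming its levels. Most secondary outcomes are to be compared by an unpaired t-test or a Mann-Whitney test, and "All categorical data will be analyzed with Chi-square test or Fishers exact test as appropriate". The significance threshold for secondary outcomes is 0.01. Hospital is not mentioned as an analysis factor.

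Results: "From June 2010 to December 2011, 57 patients were randomized". The split by hospital is not reported.

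**The concern.** When allocation is balanced within a factor, the analysis should normally contain that factor. Otherwise the difference between its levels stays in the error term, although blocking has already removed it from the treatment contrast. The standard error is then too large and the test too cautious.

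Hospital could plausibly matter here. On the staffing of the home service, the Implementation section says that "twenty experienced nurses working at the acute emergency department at Frederiksberg University Hospital were trained 4 hours each", and the Discussion adds that these nurses dealt with telemedicine patients from both hospitals. At one hospital the comparison is home care against a ward of the same institution. At the other it is remote care run from elsewhere against the local ward. Discharge is judged by the attending doctor, so bed days could also differ by hospital. None of this shows that outcomes did differ; the article gives no by-hospital figures.

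With 57 patients and a 1% threshold for secondary outcomes, avoidable loss of precision is worth removing.

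**Working it through.** **Inputs from the article:** two hospitals (Study settings); 1:1 in blocks of four, envelopes in batches of ten (Randomization); 57 randomized (Results); 23.1% readmission, margin 20%, 80% power, 20% dropout (Sample size); 0.05 primary and 0.01 secondary thresholds (Statistics). **Assumed:** hospital split 50:50 to 80:20; hospital difference d of 0, 0.5 or 1 within-hospital standard deviation (SD).

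**The plan's own figure.** n = (1.960 + 0.842)² × 2 × 0.231 × 0.769 / 0.20² = 7.85 × 0.3553 / 0.04 = 69.7, so 70 per group; 140 / 0.8 = 175. Both stated figures reproduce. They do not bear on this point.

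**Step 1: do the batches of ten upset balance?** Ten envelopes are two whole blocks and half a block. The half block falls entirely in one arm with probability 2/C(4,2) = 2/6 = 33%, which makes that batch 6:4. What follows depends on the list:
- *One list per hospital.* The next batch completes the open block. In simulation the arm difference within a hospital never exceeded 2, so batching has no effect.
- *One shared list cut into tens.* The larger of the two within-hospital arm differences averaged 1.7 to 2.2. It exceeded 2 in 21% to 35% of simulated trials and 4 in 1% to 6%.

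The article neither states nor excludes the second scheme.

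**Step 2: what does leaving out hospital cost a t-test if blocks ran within hospital?** Let π be one hospital's share and σ the within-hospital SD. The true variance of the arm difference is about 4σ²/N. The t-test estimates 4σ²[1 + d²π(1−π)]/N. Its standard error is therefore too large by k = √[1 + d²π(1−π)].
- Type I error = 2[1 − Φ(z·k)], with z = 1.960 (5%) or 2.576 (1%).
- For an effect that the adjusted analysis detects with 80% power at 5%, unadjusted power = Φ(2.802 − z·k). At 1% the adjusted analysis has Φ(2.802 − 2.576) = 58.9%.

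| Split | d | k | Type I, nominal 5% | Type I, nominal 1% | Power at 5% (adjusted 80%) | Power at 1% (adjusted 58.9%) |
|---|---|---|---|---|---|---|
| 50:50 | 0.5 | 1.031 | 4.3% | 0.79% | 78.3% | 55.8% |
| 50:50 | 1 | 1.118 | 2.8% | 0.40% | 72.9% | 46.9% |
| 80:20 | 0.5 | 1.020 | 4.6% | 0.86% | 78.9% | 56.9% |
| 80:20 | 1 | 1.077 | 3.5% | 0.55% | 75.5% | 51.1% |

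A simulation of 57 patients (100,000 trials per setting, treatment effect 0.75 SD) agrees. Type I error of the t-test at nominal 5% was 2.8% to 4.7%, against 5.0% to 5.1% with hospital in the model. The power loss was 1.1 to 7.5 points at 5% and 2.0 to 12.4 points at 1%.

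**Step 3: what does adjustment cost if hospital does not matter?** With d = 0, simulated power with and without hospital differed by less than 0.2 points.

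**Step 4: binary outcomes.** Control event rates were assumed to be 23.1% in both hospitals, 15% and 31%, or 10% and 36%, with an odds ratio of 0.15.
- Type I error at nominal 5% was 4.1% to 5.1% for the uncorrected chi-square test and 4.9% to 5.1% for Cochran-Mantel-Haenszel.
- Cochran-Mantel-Haenszel gained 0.5 to 3 points of power over a chi-square test using the same N−1 variance.
- It was 0.2 to 2.5 points below the uncorrected chi-square. This gap appears even with no hospital difference and comes from the variance formula, not from stratifying.

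Fisher's test was not simulated.

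**The case against.** The strongest objection is that this is a condensed journal article. Naming Cox strata, model levels and list structure is commonly left to a full protocol or analysis plan, and neither is shown. That stands for the regression models: the unnamed Cox stratum or mixed-model level could be hospital, and silence alone is no fault. It does not dispose of the t-, Mann-Whitney, chi-square and Fisher tests. The article states these as the chosen methods, and as named they have no place for hospital.

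A second objection is that no hospital difference is documented. Both hospitals are in the Copenhagen area, and both groups share one treatment regime and one set of discharge criteria. This is fair, and it is why the size above is conditional.

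A third is that few events are available: 57 × 0.231 is about 13 readmissions, so stratifying might cost power. For continuous outcomes the check shows practically no cost. For binary outcomes the gain is small and depends on the comparator.

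Three stronger readings are tempting, and the documents support none of them:
- A reader might infer that batches of ten broke the balance within hospital. That requires a shared list, which the text does not state.
- A reader might infer that no analysis uses hospital. Stratifying to relax proportional hazards gives a reason for stratifying; it neither names nor excludes a variable.
- A reader might infer a biased treatment estimate. Chance imbalance within hospital in a randomized trial adds noise; it does not cause systematic bias.

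**Conclusion.** The point holds in a limited form. Allocation was drawn by hospital, and the two-sample tests named for most secondary and all categorical outcomes do not use hospital. For time to readmission the omission is not shown, because the stratum is simply unnamed.

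The consequence is lost precision and a conservative test. This rests on two assumptions that the article does not settle: that blocks ran within hospital, and that hospital is prognostic. If the difference between hospitals were 0.5 to 1 SD, the t-test would lose about 1 to 8 points of power at 5%, and about 2 to 12 points at the 1% threshold set for secondary outcomes. If hospital is not prognostic, nothing is lost. If a shared list was used, balance within hospital is looser but still modest at this sample size, and adjusting for hospital remains sensible. The point is minor and does not threaten the trial's conclusions.

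**What to change.** In the Statistics section, include hospital in the comparisons:
- time to readmission: Cox model stratified by hospital, with the stratum named;
- binary outcomes: Cochran-Mantel-Haenszel test by hospital, in an exact version where Fisher's test would otherwise be used;
- continuous outcomes: linear model with hospital as a fixed effect, or a hospital-stratified rank test where Mann-Whitney would be used.

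In the Randomization section, add one sentence saying whether the blocks were generated per hospital.

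The Abstract says that results were analyzed in 2013. If the named tests have already been run, keep them as planned and report the hospital-stratified versions as labelled sensitivity analyses.

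The cost is one two-level factor that is already known for every patient, with negligible loss of power for continuous outcomes if hospital does not matter. For binary outcomes expect little change either way. No new data are needed, and no change to the envelope supply is asked for.

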### Blinding

Whereas patients and health personnel were not blinded after randomization, outcome assessors and data analysts will be blinded to the allocation, however for some of the secondary outcomes it is difficult for researchers to remain blind as the patients knew which group they were in.

### Outcomes

#### ***Primary outcome***

The primary outcome was treatment failure defined as:

Readmission due to an exacerbation in the chronic obstructive lung disease within 30 days.

Only readmissions occurring after being discharged from the telemonitoring group or the usual care group was designated a readmission. Patients in both groups were discharged when fulfilling five pre-specified discharge criteria and all telemonitoring equipment was removed from the patient’s home the same day of discharge.

#### ***Secondary outcomes***

The secondary outcomes were; 1) Prescription of additional antibiotics or steroids due to further exacerbation, 2) need of non-invasive ventilation (NIV) or mechanical ventilation, 3) death from any cause, 4) emergency room visits, 5) visits to the general practitioner, 6) lung function (FEV1, FVC, FEV1% predicted), 7) bed days, 8) health-related quality of life, 9) healthcare costs, 10) applicability, 11) user satisfaction, or 123) adverse events.

### Trial organization

One of the study doctors or a specially trained study nurse screened the electronic patient boards every morning in the emergency departments at each hospital for eligible patients. If any possible candidates had been admitted within the previous 24 hours the patients were informed in spoken and in written form about the study and were allowed one hour to decide whether they wanted to participate or not. Prior to randomization patients were treated according to the hospital’s protocol for exacerbations in COPD, which included a scoring algorithm to decide whether a patient was candidate to treatment with NIV or could continue care at the ward. The scoring system used measurements of blood gasses, oxygen saturation, the respiratory frequency and the level of consciousness to stratify the patients. In the acute phase (0 to 2 hours) all patients followed a predetermined regime monitoring arterial blood gasses, giving nebulized bronchodilator agents, oxygen therapy, corticosteroids and antibiotics in fixed doses by the attending doctor. After the acute phase it was determined through the scoring algorithm whether the patient needed intensive care (NIV/manual ventilation), continued care at a hospital ward, or could be discharged from the hospital. The patients who needed continued care at the ward were thereafter asked to participate in the trial.

